#### Secondary outcomes

Secondary outcome measures describing postpartum blood loss

#### Clinical

mean gravimetrically estimated blood loss, by measuring the suction volume and swab weight according to Gai et al. (estimated blood loss = (weight of materials used + materials not used - weight of all materials before surgery)/1.05 + volume included in the suction container) [23, 27, 28], recorded from placental delivery to:
▪ the end of the cesarean delivery, and just before the woman’s transfer to the PACU.▪ the discharge of the woman from PACU (i.e., about 2 h after the end of the cesarean delivery).gravimetrically estimated blood loss > 500 mLgravimetrically estimated blood loss > 1000 mLincidence of provider-assessed clinically significant PPH, defined by the providers’ response to the question: “Was there a PPH?” [22, 39]proportion of women requiring supplementary uterotonic treatment, including sulprostone [22, 39]incidence of postpartum transfusion (until discharge) [22, 39]mean number of RBC units transfusedincidence of iron sucrose perfusion (until discharge from hospital)incidence of arterial embolization and emergency surgery for PPH [22, 39].incidence of hypovolemic shock related to PPHincidence of transfer to ICUincidence of maternal death from any cause [22, 39].

#### Laboratory

incidence of calculated blood loss > 500 mL and > 1500 mLmean total calculated blood lossmean peripartum change in hemoglobin (difference between hemoglobin before delivery and at D2) [22, 39]Hemoglobin drop > 2 g/dL (between hemoglobin before delivery and at D2) [22, 39]

For all laboratory indicators, the predelivery reference examination will be the most recent blood count obtained within 1 week before delivery. As previously described [22, 39], all patients included in the trial will provide a blood sample on the second day postpartum (D2) to measure their peripartum hemoglobin and hematocrit and calculate the change in these two indicators. If no blood sample is available from D2, these measurements will be assessed from a D3 blood sample, if available. If no blood sample is available from D2 or D3, they will be assessed from the blood sample closest to D2 in the absence of transfusion.
The occurrence of potential adverse effects of tranexamic acid, most as previously reported (39), with some modifications:

#### Clinical

Hemodynamic parameters (heart rate, blood pressure) 15, 30, 45, 60, and 120 min after delivery [22, 39].the occurrence of potential mild adverse effects of tranexamic acid in the operating room:
▪ nausea▪ vomiting▪ phosphenes▪ dizzinessthe occurrence of potential severe adverse effects of tranexamic acid during the hospital stay and up to 12 weeks postpartum [22, 39]:
▪ deep vein thrombosis, if the diagnosis is confirmed by Doppler ultrasound [39]▪ pulmonary embolism, if the diagnosis is confirmed by radiological examination [39].▪ myocardial infarction [39]▪ seizure [39]▪ renal failure requiring dialysis [39]▪ any other unexpected adverse events [39].

As previously [39], these events will be checked by the medical team during the hospitalization and then at 12 weeks postpartum by a telephone interview of each woman. In the event that the woman cannot be reached, at least 10 calls at different hours over the course of the week will be made to minimize loss to follow-up. In cases of severe adverse effects reported by a woman after discharge, objective data will be collected from medical files, transmitted either by the woman herself or her general practitioner.

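### After discharge, the active search for severe harms depends on the woman answering the 12-week call, and the only stated fallback is more calls to her

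*Protocol article*

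**What the plan says.** The adverse-effects list under Secondary outcomes (Clinical) in the protocol article covers severe events during the hospital stay and up to 12 weeks postpartum. In hospital, the medical team checks for them. After discharge they are checked "then at 12 weeks postpartum by a telephone interview of each woman". The rule for a woman who does not answer is: "In the event that the woman cannot be reached, at least 10 calls at different hours over the course of the week will be made". The rule for obtaining records begins "In cases of severe adverse effects reported by a woman after discharge, objective data will be collected from medical files", and those files are "transmitted either by the woman herself or her general practitioner".

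Two events carry a diagnostic condition: "deep vein thrombosis, if the diagnosis is confirmed by Doppler ultrasound" and "pulmonary embolism, if the diagnosis is confirmed by radiological examination". Myocardial infarction, seizure, dialysis and other events carry none.

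Data management confirms that the clinical research technician (CRT) fills in the 12-week form during the call with the woman. The 8-week questionnaire described there covers satisfaction and psychological status, not harms.

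Safety consideration describes another route. The local coordinator sends a form within 72 h for a list that includes maternal death, surgery within 12 weeks of randomization, ICU admission, deep vein thrombosis (DVT), pulmonary embolism (PE), myocardial infarction, seizure and dialysis. Maternal death from any cause is also a secondary outcome, with no time window or data source given in that item.

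**The concern.** Every step of the active search after discharge starts from the woman. She must take the call, and she must report the event before anyone looks for a file. A woman who has died cannot do either, and one who is gravely ill in the week of the calls is unlikely to. Repeating the calls does not help in those cases. Whether the 12-week status is known may therefore depend on the outcome itself.

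This matters because the Discussion sets the aim as weighing benefit against risk, and Objectives names any venous or arterial thrombosis in the 3 months after delivery as a safety question. The Background criticizes earlier cesarean trials for attrition bias and for too little power on severe adverse events. With rare events, each one that is not found costs information.

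**Working it through.** **The plan's own figures.** The article gives no figure for post-discharge harms. Its sample size supplies only the denominator. The stated 2036 per group reproduces for 15% vs 12% (two-sided 0.05, power 0.80, pooled variance), and 2036/0.90 = 2262.2 against the stated 2262 per group (4524 in total). The 10% allowance covers cancelled cesareans, loss to follow-up and missing postpartum blood samples for the primary outcome. It is not a 12-week loss rate.

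**Routes by which an event after discharge can become known:**

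| Route | What starts it | Works if the woman is never reached? |
|---|---|---|
| 12-week interview | she answers | no |
| Repeat calls | she answers | no |
| Medical files | she reports an event | no |
| Coordinator's safety form | the center learns of the event | only if word reaches the center |

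The first three rows are one route in three stages. The fourth is independent of the call but passive after discharge: no search for events treated elsewhere is described, and no link to the outcome data is stated.

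**Scale, on assumptions.** Let L be the proportion unreached, k the risk in unreached relative to reached women, and p the overall event risk. None of these is in the article. I use L = 2%, 5%, 10%; k = 1 or 5; p = 0.1% to 0.4%.

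- Unreached women per arm: 2262 × L = 45, 113, 226.
- Expected events per arm: 2262 × p = 2.3 to 9.0.
- Share of all events that fall in unreached women: s = Lk / (Lk + 1 − L).
- Events at risk of being missed, per arm: 2262 × p × s.

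| L | k | s | Events at risk per arm, p = 0.1% | p = 0.4% |
|---|---|---|---|---|
| 2% | 1 | 2% | 0.05 | 0.18 |
| 2% | 5 | 0.10/1.08 = 9% | 0.21 | 0.84 |
| 5% | 1 | 5% | 0.11 | 0.45 |
| 5% | 5 | 0.25/1.20 = 21% | 0.47 | 1.9 |
| 10% | 1 | 10% | 0.23 | 0.90 |
| 10% | 5 | 0.50/1.40 = 36% | 0.81 | 3.2 |

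These are upper limits: they take every event as arising after discharge and none as reaching the center by another route.

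**Effect on the estimates, if s is the same in both arms.**

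- Absolute rate, unreached women kept in the denominator as event-free: multiplied by 1 − s. For k = 5 this is 0.79 at L = 5% and 0.64 at L = 10%.
- Absolute rate, unreached women left out of the denominator: multiplied by 1/(1 − L + Lk). For k = 5 this is 1/1.20 = 0.83 and 1/1.40 = 0.71. For k = 1 there is no bias.
- The absolute risk difference, which Statistical analysis promises for binary outcomes, shrinks by the same factor.
- Risk ratio: the factor cancels, so its expected value is unchanged.
- Standard error of the log risk ratio, approximately √(1/a + 1/b) for a and b events: multiplied by 1/√(1 − s), that is 1.12 for s = 21% and 1.25 for s = 36%.

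**The case against.** The best counter-argument is that the telephone is not the sole route. The coordinator's form covers death, thrombosis and the other severe events without depending on the call, and its reference to surgery within 12 weeks shows that it extends past discharge. This stands, and it rules out any claim that harms are recorded only when the phone is answered. It does not close the gap, because nothing obliges anyone to look for events the center has not heard of.

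Second, a reader might infer that events without a file, or women without an interview, disappear from the safety result. The article does not say so. It says that objective data will be collected, and it names the GP as an alternative source. The imaging condition applies only to DVT and PE, and it concerns the diagnosis, not whether the trial holds the report. How missing 12-week status is analyzed may be set out in the full protocol or SAP. All this stands. But the article itself fixes the tracing rule, down to the number of calls, and no analysis recovers an event that was never found.

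Third, most women with a thrombosis in the early weeks will be able to report it at week 12. This also stands: the outcome-related part of the problem concerns women who died or were incapacitated, with ordinary non-response added.

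Fourth, a reader might infer that a few lost events would bias the risk ratio or hide a real excess. The trial is double-blind and nothing in the article suggests that loss differs by arm. Losing a third of one arm's events would need k = (1 − L)/(2L), that is 4.5 at L = 10% or 9.5 at L = 5%, with no loss in the other arm. The documents do not support that reading.

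**Conclusion.** The point holds as a weakness in ascertainment. After discharge, the active search cannot find an event in a woman who is never reached, and the one independent route is passive and not stated to feed the outcome data. The consequence that can be supported is under-counted absolute rates and lost precision for rare harms. A bias in the ratio between arms is not shown.

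The size is unknown, because the article gives no 12-week loss rate, no event rate and no risk for unreached women. On the assumed ranges, the share of events at risk runs from 2% (2% unreached, equal risk) to 36% (10% unreached, five times the risk), or from well under one event to about three per arm. The primary outcome and the sample size are unaffected.

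**What to change.** Amend the follow-up paragraph of the adverse-effects subsection under Secondary outcomes as follows:

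1. If the calls fail, the CRT checks the maternity hospital's own record for readmission, imaging that confirms thrombosis, and death, and contacts the GP for vital status and events.
2. Events reported under Safety consideration are reconciled with the 12-week outcome data.
3. DVT or PE reported without an imaging report is listed separately, by arm.
4. The number of women with unknown 12-week status is given by arm.

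The cost is a record check and a GP contact by existing CRTs, for unreached women only (90 to 452 across both arms at 2% to 10% of 4524), and a sentence in the consent form if this access is not already covered. No visit, test or treatment changes.

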#### Laboratory

mean urea and creatinemia, prothrombin time (PT), active prothrombin time (aPTT), aspartate and alanine transaminase, and total bilirubin at D2 [22, 39].
Women’s satisfaction and psychological status
This will be assessed by a self-administered questionnaire on D2 postpartum and by mail or email at 8 weeks postpartum [22, 39].

### Statistical analysis

As in our previous TRAAP study of vaginal deliveries [22, 39], data analysis and reporting will adhere to the CONSORT guidelines for randomized controlled trials and will be conducted with the trial statistician and researchers blinded to group status. The women’s demographic characteristics and standard risk factors for PPH will be compared between the two groups. The main analysis of the primary and secondary outcomes will be performed in the modified intention-to-treat (ITT) population, defined as women who undergo randomization and have a cesarean delivery (except if they withdraw consent or are deemed ineligible after randomization). We will also analyze two separate per-protocol populations: women from the modified ITT population receiving a uterotonic and then tranexamic acid or placebo in the 3 min after delivery (as prespecified in the protocol) (per-protocol group 1); the other will include women from the modified ITT population receiving a uterotonic and then tranexamic acid or placebo in the 10 min after delivery (per-protocol group 2; for a situation more consistent with routine clinical practice).

The baseline characteristics of the trial participants, the management of the third stage of labor, and protocol adherence will be compared by descriptive statistics. Quantitative variables will be expressed, as appropriate, as means with standard deviations (and compared by Student’s t-test) or as medians with interquartile ranges (compared by the Wilcoxon rank-sum test). Chi-square or Fisher’s exact tests will be used, as appropriate, to compare categorical variables. The effects of tranexamic acid will be expressed as relative risks with 95% confidence intervals for categorical outcomes and as mean differences with 95% confidence intervals for quantitative outcomes. The results will also be expressed as absolute risk differences with 95% confidence intervals for binary outcomes.

Two prespecified subgroup analyses will examine the primary outcome in subgroups of women at high risk of postpartum hemorrhage. The subgroups will include women who undergo a cesarean during labor and those who are at risk for postpartum hemorrhage according to a composite definition (having at least one risk factor with an odds ratio of 3 or greater in the literature [53]: history of any of postpartum hemorrhage, pregnancy-related hypertensive disorder, multiple pregnancy, or cesarean during labor). Moreover, prespecified subgroup analyses will examine the secondary outcomes in the subgroup of women who undergo a cesarean during labor. We will use the Benjamini–Hochberg procedure to adjust for multiple comparisons of secondary outcomes or subgroups.

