#### Objectives

The aim of this study is therefore to compare the effect of the administration of a low dose of tranexamic acid (1 g) in the 3 min after a cesarean delivery with placebo, both in addition to prophylactic uterotonics, in a multicenter randomized, double-blind, placebo-controlled trial with two parallel groups.

The specific object ives, similar to but modified from those for the TRAAP trial for vaginal deliveries [22, 39], are as follows:
To assess the effect of tranexamic acid (1 g) on postpartum blood loss after cesarean delivery
Primary outcome
Incidence of PPH defined by a calculated estimated blood loss > 1000 mL [Calculated estimated blood loss = estimated blood volume × (preoperative hematocrit - postoperative hematocrit)/preoperative hematocrit (where estimated blood volume (mL) = weight (Kg) × 85)] or red blood cell (RBC) transfusion before day 2 (D2) postpartum [5–7]. Preoperative hematocrit will be the most recent hematocrit within 1 week before delivery. Postoperative hematocrit will be measured at D2 (see below).Secondary outcomes
Other outcome measures describing postpartum blood loss, including but not limited to calculated blood loss > 500 mL, > 1500 mL and mean total calculated blood loss, mean gravimetrically estimated blood loss by measuring the suction volume and swab weight until discharge from the post-anesthesia care unit (PACU) (i.e., about 2 h after the end of the cesarean) [23] as well as > 500 mL and > 1000 mL; mean gravimetrically estimated blood loss at the end of the cesarean delivery, mean or median number of units of red blood cells transfused, incidence of postpartum iron perfusion, shock, as well as the outcomes previously considered [22, 39]: provider-assessed clinically significant PPH, proportion of women requiring supplementary uterotonic treatment including sulprostone, incidence of postpartum transfusion, incidence of arterial embolization or emergency surgery for PPH, mean peripartum change in hemoglobin and hematocrit as well as hemoglobin drop > 2 g/dL, transfer to intensive care unit (ICU), or death from any cause.To assess the potential adverse effects of tranexamic acid (1 g) after cesarean delivery:
Hemodynamic parameters, adverse gastrointestinal events, renal, hepatic, and coagulation function, and any venous or arterial thrombosis in the 3 months after delivery (39).To assess women’s satisfaction and psychological status at D2 and D60 [39].

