### Sample size

We assumed a 15% incidence of our primary outcome (calculated blood loss > 1000 mL or RBC transfusion before D2) after cesareans in the absence of tranexamic acid, based on the results from a high-quality RCT conducted in the Republic of Ireland with a similar outcome measure (*n* = 2069) [5]. To show a relative reduction of at least 20% in the incidence of postpartum hemorrhage in the tranexamic acid arm — that is, an incidence of 12% or less in this arm, with α = 0.05, 1 − β = 0.80, and a bilateral test, the study will require 2036 women with a cesarean delivery in each group, totaling 4072 participants. A higher number of randomized women must be included given that some will have a scheduled cesarean cancelled, be lost to follow-up, or lack the postpartum blood sample needed to assess the primary outcome (estimated at a maximum of 10%). Accordingly, we plan to include 2262 women in each group, totaling 4524 participants.

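### The main analysis of adverse effects uses a modified ITT set that can drop a dosed woman found ineligible after randomisation, even when her adverse event prompted the finding

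*Protocol article*

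**What the plan says.** Under Statistical analysis, the protocol article states: "The main analysis of the primary and secondary outcomes will be performed in the modified intention-to-treat (ITT) population". That set is "defined as women who undergo randomization and have a cesarean delivery (except if they withdraw consent or are deemed ineligible after randomization"). The text does not say when ineligibility must be established, on what information, or whether a woman who has already received the vial can still be removed.

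The only other sets named are per-protocol: "We will also analyze two separate per-protocol populations: women from the modified ITT population receiving a uterotonic" and then the study drug within 3 or 10 minutes of delivery. A woman missing from the modified ITT set is missing from both.

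Adverse effects form one of the outcome groups under the Secondary outcomes heading, introduced by "The occurrence of potential adverse effects of tranexamic acid, most as previously reported (39), with some modifications". The severe ones (deep vein thrombosis, pulmonary embolism, myocardial infarction, seizure, dialysis and other unexpected events) are followed to 12 weeks. Safety is also a stated aim: the Objectives include "any venous or arterial thrombosis in the 3 months after delivery".

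**The concern.** Some exclusion criteria cover the same clinical ground as the safety outcomes. A woman with a previous thrombosis or seizure should not be enrolled, and thrombosis and seizure are what the safety follow-up looks for. If such a history is missed at enrolment, working up an event is one of the occasions on which it can surface. She then meets the wording for removal although she was randomised, dosed and had the event.

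Removal then depends on the outcome. What is at stake is the between-group comparison of rare harms, in a trial whose Discussion sets out to weigh benefits against risks and whose Background faults earlier trials for too little power on severe adverse events.

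**Working it through.** **1. Does the rule reach adverse effects?** Secondary outcomes are assigned to the modified ITT set (Statistical analysis). Adverse effects stand under Secondary outcomes. Both per-protocol sets are drawn from the modified ITT set. So no set named in the article keeps a dosed woman who is later found ineligible.

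**2. Can an event lead to removal?** Setting the Exclusion criteria beside the adverse-effects section:

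- History of thrombosis, history of epilepsy or seizure, and autoimmune disease are listed without the qualifier *known*. A history found later still makes the woman ineligible in retrospect.
- Cardiovascular, renal and liver disorders are limited to known active disease. A disorder first discovered during work-up does not clearly breach these criteria, so the mechanism is weak there.
- For severe effects reported after discharge, records are obtained through the woman or her general practitioner. The article describes no such retrieval for women without an event. History held outside the obstetric file is therefore more likely to be found in women who had one.

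**3. Direction of the bias.** Let p1 and p0 be the true event risks on active and placebo, and f1 and f0 the fractions of women with events who are removed. The risk in the modified ITT set is p(1 − f)/(1 − pf), which is close to p(1 − f) for rare events.

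- Risk difference, if f1 = f0 = f: (1 − f)(p1 − p0). Any excess on the drug shrinks towards zero.
- Risk ratio: (p1/p0) × (1 − f1)/(1 − f0). With equal fractions its expectation is roughly unchanged and only events are lost. It moves towards 1 when f1 > f0, for example if the drug's excess falls mainly on women with an undetected excluded history.

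The article will report both measures.

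**4. Number of events.** The planned arm size reproduces. "We assumed a 15% incidence of our primary outcome", against "an incidence of 12% or less in this arm, with α = 0.05, 1 − β = 0.80, and a bilateral test", gives, with pooled variance:

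- n = [1.960 × √(2 × 0.135 × 0.865) + 0.842 × √(0.15 × 0.85 + 0.12 × 0.88)]² / 0.03² = 2036 per arm.
- 2036/0.90 = 2262.2; the article states 2262.

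The article gives no severe-event risk, so the following risks are assumptions:

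- 0.05%: 0.0005 × 2262 = 1.1 events per arm
- 0.1%: 0.001 × 2262 = 2.3
- 0.3%: 0.003 × 2262 = 6.8

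**5. Effect of removals.** Counts are assumed, and all removals are from the active arm:

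| Events, active vs placebo | RR, none removed | 1 removed | 2 removed | 3 removed |
|---|---|---|---|---|
| 8 vs 1 | 8.0 | 7.0 | 6.0 | 5.0 |
| 8 vs 2 | 4.0 | 3.5 | 3.0 | 2.5 |
| 6 vs 2 | 3.0 | 2.5 | 2.0 | 1.5 |

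For 8 vs 1 with one removed: (7/2261)/(1/2262) = 7.0. The risk difference falls from 7/2262 = 0.31% to 7/2261 − 1/2262 = 0.27%.

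**6. P values.** For 8/2262 vs 1/2262, two-sided Fisher P = 0.039. The removed woman leaves the denominator too, and 7/2261 vs 1/2262 again gives P = 0.039. A value of 0.070 arises only from 7/2262 vs 1/2262, or from doubling the one-sided P. The unchanged 0.039 reflects how the two-sided exact test treats nearly tied tables. The example cannot support a statement about significance.

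**The case against.** The strongest reply is that this is really a missing safety set, which a journal article may leave to the full protocol or SAP. It is true that the article fixes only the main analysis, that an unseen document may define a safety population, and that the Objectives list adverse effects apart from the secondary outcomes on blood loss. But the article does more than stay silent: it assigns secondary outcomes, with adverse effects among them, to a set with this exclusion. The point rests on that assignment.

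Second, several safeguards exist.

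- Allocation is masked, and analysis "will be conducted with the trial statistician and researchers blinded to group status". This prevents deliberate selection by arm. It does not stop removals from following events.
- Severe events are reported individually, go to the Safety Monitoring Committee, and can be unblinded. An interim safety analysis is planned. Cases would therefore be seen; what suffers is the comparison between groups.
- CONSORT reporting should show post-randomisation exclusions by arm.
- The obstetric file is abstracted for every woman, so a history recorded there can be found whatever the outcome.

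Third, a reader might infer more than the text supports:

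- *That such women will be removed.* The text permits it. It does not say that an event reopens eligibility, and nothing in the article indicates how often it would.
- *That one removal would overturn a significant safety result.* The Fisher calculation does not show this. Eight or more events in one arm at a 0.1% risk has Poisson probability of only about 0.002, so the 8 vs 1 example already presupposes marked harm. Secondary outcomes are also adjusted by Benjamini–Hochberg.
- *That the efficacy result is compromised in the same way.* Abruption or invasive placenta seen at surgery is a pre-existing condition judged under masked allocation, and the vial is given only after birth and cord clamping. Removing a few such women barely affects an outcome expected in 12–15%.

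**Conclusion.** The concern holds as a fault in a stated analysis rule. As written, the main comparison of adverse effects can lose a dosed woman because of her own event, and no other named set restores her. The route is credible for prior thrombosis, prior epilepsy or seizure, and autoimmune disease, and weak for the criteria limited to known active disorders.

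A shift towards no harm requires a real excess of events on the drug, an excluded history missed at enrolment, and a decision to exclude. Under equal removal fractions it affects the risk difference; for the risk ratio it also needs proportionately more removals on active. The frequency is unknown. The size per removal depends on assumed counts: with 1 to 7 events per arm, one removal moves the estimate visibly, but nothing follows about significance. The sample size is unaffected. The wording should be corrected because the loss is avoidable at almost no cost.

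**What to change.** State that all adverse effects are analysed in every randomised woman who received any study drug, by the product received, whatever is later learned about her eligibility, and up to any withdrawal of consent. The modified ITT set can remain the main set for efficacy.

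Optionally, for efficacy, restrict ineligibility exclusions to facts that existed before randomisation, judged blind to arm and outcome, and add a sensitivity analysis that retains these women.

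The cost is a change of wording and a second denominator in the safety tables, which needs a footnote. No new data, visits or procedures are required.
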